## Abstract

**Background:**

Depression and alcohol misuse represent two of the major causes of disease burden in young adults. These conditions frequently co-occur and this co-occurrence is associated with increased risks and poorer outcomes than either disorder in isolation. Integrated treatments have been shown to be effective, however, there remains a significant gap between those in need of treatment and those receiving it, particularly in young people. The increased availability of Internet-based programs to complement health care presents a unique opportunity in the treatment of these conditions.

**Objective:**

The objective of our study was to evaluate whether a brief, Internet-based, self-help intervention (the DEAL [DEpression-ALcohol] Project) can be effective in treating co-occurring depression and problematic alcohol use in young people (18-25 years old).

**Methods:**

The evaluation will take the form of a randomized controlled trial (RCT), comparing the DEAL Project with an attention-control condition (HealthWatch). The RCT will consist of a four-week intervention phase and a 24-week follow-up. It will be entirely Internet-based and open Australia-wide to young people 18 to 25 years old. The primary outcomes will be change in depression symptoms and alcohol use at 5, 12, and 24 weeks post baseline. Secondary outcomes include change in general functioning and quality of life, anxiety/stress symptomatology, and a number of other depression/alcohol related outcomes. Process analysis will also measure engagement across the conditions.

**Results:**

This study is currently ongoing with preliminary results expected in late 2014.

**Conclusions:**

This study, to our knowledge, will be the first RCT of a Internet-based treatment for comorbid depression and problematic alcohol use in any age group. If successful, the program represents a novel and innovative approach to addressing the significant harms associated with these conditions and will be an invaluable resource to those not receiving help elsewhere.

**Trial Registration:**

Australian New Zealand Clinical Trials Registry; ACTRN12613000033741;
https://www.anzctr.org.au/Trial/Registration/TrialReview.aspx?id=363461 (Archived by WebCite at http://www.webcitation.org/6Mrg9VFX4).

## Introduction

### Alcohol Use Disorders and Depression

In the developed world, two of the top five leading global causes of years lost to disability are alcohol use disorders (AUD) and depression [1]. Young people bear a disproportionately large share of these burdens [2,3]. In Australia, the highest prevalence of 12-month AUDs in any age bracket occurs in those 16-24 years old (11.1%) [4]. In addition, this age bracket has the highest incidence rates for depression of any age group [5], half of whom will experience recurrent episodes of depression [6].

### Comorbidity

Comorbidity across the disorder classes is common. Approximately one in four (22.2%) young Australians (16-25 years old) with current major depression also meet criteria for a 12-month AUD, while 14.3% of those with a 12-month AUD meet criteria for current major depression [7]. In treatment samples, rates of comorbidity are as high as 89% [8].

These comorbid conditions are associated with increased suicidality [9-11], symptom severity, and poorer social, interpersonal, and general functioning compared to those with a single disorder [12-14]. This group is also likely to report poorer quality of life [15] and increased treatment reliance [16-21]. Furthermore, these disorders tend to maintain and exacerbate one another [22]. As such, in recent years there has been increasing support for integrated approaches to comorbidity [23,24]. Baker et al [25] have demonstrated that concurrent treatment of depression and problem drinking is more effective than treating either condition alone and more effective than general counseling.

Hides et al [26], suggest that treatment integration is particularly relevant to youth, given “coping” is a key motive for substance use among young people with mental health issues. There have, however, been few such attempts made in younger populations [27-29]. Although early intervention is imperative to averting the development of more severe, ingrained morbidity [30,31], fewer than 25% of affected young people access traditional health services in a 12-month period [32].

### Internet-Based Interventions

Internet-based interventions have been deemed to be particularly useful for those less likely to access traditional services, such as young people [33]. Advantages of these interventions include flexibility, anonymity, and accessibility, and as such, have the potential to overcome a number of structural and attitudinal barriers that frequently limit help seeking efforts in this population [34,35]. Furthermore, Internet use is widespread among young people [36,37]. Research suggests that the Internet helps to empower young people [38], and that young people are comfortable accessing both general health information and seeking specific mental health treatment via this medium [39,40]. Additionally, Internet-based treatments have the potential to reduce costs associated with treatment (by reducing contact time with the therapist), and increase treatment standardization and adherence to evidence-based practice [41,42]. Finally, this modality has also been shown to overcome imbalances in treatment seeking, access, and availability [43,44].

Such interventions have been shown to be effective and cost effective in treatment for depression and related disorders [45,46]. A number of recent meta-analyses have indicated that effect sizes for such interventions are small to moderate (0.28-0.78) [47-50], but roughly equivalent to traditional face-to-face therapy [51,52]. Similarly, recent meta-analyses have indicated that effect sizes for such alcohol interventions are small to moderate (0.22-0.48) [33,48, 53-55], again not dissimilar to brief in-person interventions [56,57].

To our knowledge, there has been no youth-focused Internet-based comorbidity interventions. Furthermore, in the general population only one computerized comorbidity intervention targeting these disorders has been evaluated. These evaluations of the computerized Self Help for Alcohol/other drug use and Depression (SHADE) resource indicate electronic forms of treatment for co-occurring disorders are viable and effective [58,59]. In two randomized controlled trials (RCTs), the SHADE program was associated with equivalent outcomes to that achieved by therapist-delivered treatment, with superior results as far as reducing alcohol consumption over 3- and 12-months.

Although unguided Internet-based interventions may not always be as effective as a face-to-face encounter with a skilled clinician, the reality is that a majority of those with depression and alcohol problems (especially young people) will never receive any face-to-face intervention. Fewer still will see a skilled clinician [32,60]. Internet-based interventions have the potential to engage young people through the use of new, interactive technology and may overcome the stigma associated with seeing a therapist.

### Objective

The primary aim of the study is to evaluate whether a brief, Internet-based intervention—the DEpression-ALcohol Project (DEAL)—can be effective in treating co-occurring moderate depression and problematic alcohol use in young people (18 to 25 years old). This evaluation will take the form of a RCT comparing the DEAL Project to an attention-control condition and measuring participant outcomes across time. This will be, to our knowledge, the first RCT of an Internet-based treatment for comorbid depression and problematic alcohol use in any age group.

## Methods

### Study Setting

The study will be conducted Australia-wide and entirely Internet-based with minimal participant contact. All contact made will occur via email, with the exception of follow-up contact from a clinical psychologist if participants report experiencing particular distress and are suicidal (see Safety Protocol).

### Study Design

The proposed RCT meets international standards for such trials. Figure 1 shows the design of the study and intended flow of participants. Initial contact with potential participants will be made via the Internet. Upon visiting the website, potential participants will complete an initial screening to determine eligibility. Eligible participants will receive a follow-up email to complete the full Internet-based baseline assessment, with randomization to one of the two treatment groups following assessment. Following randomization, participants will be provided with their login access code along with instructions about how to access the treatment website. Follow-up Internet-based assessment will occur across the two conditions at 5, 12, 24 weeks post baseline.

**Figure 1 figure1:**
[figure not shown]
Flow of participants through the study.

### Ethical Approval and Registration

The study is registered with the Australian New Zealand Clinical Trials Registry (ACTRN12613000033741) and has ethical approval from the University of New South Wales Human Research Ethics Committee (HC12546). Consent will be obtained electronically from all participants and confidentially assured via rigorous data encryption.

### Participants

We will aim to recruit approximately 200 participants. The trial has a purposive sample of young people reporting drinking at harmful levels with mild to moderate depressive symptoms. Young people will be informed that the study compares an Internet-based self-help program for depression and alcohol use with a healthy lifestyles program on a range of outcomes, and they will be randomly allocated to one of these groups. Recruitment will be Australia-wide, using extensive media coverage; including tertiary institutions and street press, Internet-based chat forums and blogs, government, youth-oriented services and websites, and paid Facebook and Google advertisements. The research team has been successful using similar strategies in previous studies [61]. They also have extensive experience recruiting large samples of participants with depression and alcohol use comorbidity (eg, 558 in 24 months in two states) [25,59].

### Inclusion and Exclusion Criteria

Inclusion criteria include: (1) 18-25 years old, (2) current depressive symptoms (score of ≥7 on Depression Anxiety Stress Scale-21-DASS-21-Depression) [62], (3) harmful drinking as measured by the Alcohol Use Disorders Identification Test (AUDIT) (score of ≥8) [63,64], (4) ability to access the Internet (either in the private residence of the participant, or willingness to use the public library/other suitable venue with Internet access), and (5) Australian residency.

Exclusion criteria include: (1) psychotic symptoms screener score ≥3 [65], (2) non-English speakers, (3) serious risk of suicide (serious past 2-week thoughts of suicide and desire to act), and (4) daily use of cannabis/weekly use of amphetamines.

### Randomization

Randomization will be automated within the program and therefore trial researchers will be blind to it. This process will occur immediately after the eligibility screener and baseline assessment have been completed and consent provided.

### Safety Protocol

In any trial concerned with mental health or substance use there is the potential to uncover psychological distress in participants. In this population there is an increased risk, as the participants are mild-moderately depressed and drinking at harmful levels. As recruitment (and the trial itself) is entirely Internet-based, no contact (other than email) will occur between participants and the research team during the course of the study. In order to minimize risk, study participants will be provided with a contact email of a clinician upon commencement of the trial. A trained clinical psychologist and member of the research team will monitor this email. Upon email contact, the psychologist will make contact with the participant and initiate a dialogue and negotiate local referral options where appropriate.

Upon weekly login, participants will answer a screening question regarding suicidality (thoughts of suicide or a wish to commit suicide in the past week). On the basis of their answer, they are prompted to the email contact of the psychologist.

At the beginning and end of each periodic assessment, the participant will again be presented with this referral information for crisis care.

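### The Safety Protocol answers a positive weekly suicidality answer only with a prompt to write to the psychologist, and does not clearly carry out the follow-up that Study Setting refers to it

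*Protocol article*

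**What the plan says.** Two sections of the protocol article's Methods govern contact with participants at risk.

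**Study Setting** limits contact to email, "with the exception of follow-up contact from a clinical psychologist if participants report experiencing particular distress and are suicidal", and refers to the Safety Protocol for this exception.

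**Safety Protocol** sets out these steps:

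- Contact in general: "no contact (other than email) will occur between participants and the research team during the course of the study". No exception is attached, and the psychologist is described as belonging to the research team.
- At entry: "study participants will be provided with a contact email of a clinician upon commencement of the trial". The psychologist monitors that mailbox.
- When a participant writes: "Upon email contact, the psychologist will make contact with the participant and initiate a dialogue", with local referral where appropriate.
- Each week: "Upon weekly login, participants will answer a screening question regarding suicidality", covering suicidal thoughts or a wish to die by suicide in the past week. The response is: "On the basis of their answer, they are prompted to the email contact of the psychologist".
- At the start and end of each periodic assessment: "the participant will again be presented with this referral information for crisis care".

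**The concern.** The trial puts a suicidality question to participants at weekly login, so it will receive disclosures. As the Safety Protocol is worded, the next move after a disclosure belongs to the person at risk, who is shown an address and has to write to it. Study Setting suggests something more active.

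The article's own rationale makes this matter. It links this comorbidity to increased suicidality, states that fewer than 25% of affected young people use traditional health services in a 12-month period, and presents Internet delivery as a way round barriers to help seeking. A response that depends on the participant seeking help leans on a behaviour that the Introduction describes as often lacking.

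What is at stake is participant safety, and whether the study team would act the same way whichever of the two sections it followed.

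**Working it through.** No formula applies and the plan gives no figure to reproduce. The check is a comparison of the two sections.

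**1. What triggers psychologist contact?** In Study Setting, the trigger is a participant reporting distress and being suicidal. In the Safety Protocol, it is an email from the participant. Whether these are the same depends on what counts as a report, so both readings are followed through.

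**2. Reading A: a positive weekly answer is a report.** Study Setting then describes psychologist follow-up after that answer. The Safety Protocol's stated response is a prompt only. The section cited for the follow-up does not provide it.

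**3. Reading B: reporting means writing to the psychologist.** The two sections then agree on the trigger, and the contact made after the email is the follow-up that Study Setting means. A participant who discloses at login but does not write then has no stated outreach in either section.

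| Participant | Reading A | Reading B |
|---|---|---|
| Positive answer, writes | Psychologist contact stated | Psychologist contact stated |
| Positive answer, does not write | Described in Study Setting, not provided in Safety Protocol | No outreach stated |

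The second row is unsatisfactory on either reading.

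**4. Do the other steps cover that row?** The address given at entry and the referral information at assessments are useful, but both need the participant to act.

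**5. Does the entry exclusion cover it?** No. Inclusion and Exclusion Criteria removes people with serious suicidal thoughts in the previous two weeks together with a desire to act. The weekly question is broader, so someone below the entry threshold can enrol and later answer positively, and anyone can worsen after entry.

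**6. Is the email-only sentence consistent?** Study Setting has an exception and the Safety Protocol has none. Because the psychologist is named as a team member, the Safety Protocol's sentence, read literally, confines the psychologist to email too. This holds on both readings.

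**7. Are the means to act already there?** The program must read the weekly answer in order to prompt on it. Administration of Assessments requires an email address at commencement and sends a reminder when an assessment is six days late. A psychologist is on the team.

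**The case against.** The strongest objection is that this is a condensed article. A step-by-step escalation procedure is the kind of detail that is left to a full protocol, and the study has ethics approval. Read as a whole, the document does commit to psychologist follow-up in Study Setting, and a positive weekly answer can naturally be taken as a report. The Safety Protocol's line about the psychologist making contact may be the very exception that Study Setting has in mind. On that view only an unrepeated clause is left to correct.

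Much of this stands. A reader might infer that the trial has no outreach, or that the two sections flatly contradict each other. The document supports neither: Study Setting states an intention to follow up, nothing rules outreach out, and Reading B reconciles the trigger.

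What does not stand is that this is only missing detail. The article states the response to a positive answer and the condition for psychologist contact. Followed as written, these leave a participant who discloses but does not write without a stated contact.

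Two smaller objections are fair. An overdue-assessment reminder is administrative; it shows that an automatic email is technically possible, not that clinical outreach is equally simple. The Discussion also plans to collect contact details of significant others, so email may not be the only route to a participant. Those details are meant for locating people for follow-up assessments, and the fix does not need them.

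**Conclusion.** The point holds in limited form. The Safety Protocol, as stated, does not clearly carry out the follow-up that Study Setting refers to it. On the reading that reconciles the two, participants who disclose without writing have no stated outreach. The missing exception in the email-only sentence is a separate, minor inconsistency.

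**Size.** The rule covers the approximately 200 planned participants in both arms. That is its reach, not the number affected: neither the rate of positive answers nor the share who would not write can be derived from the document. Sample size, power and error rates are untouched.

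**Assumptions.** The conclusion rests on the published wording alone. A fuller protocol, not shown, may already contain a team-initiated step; the remedy would then be to bring this text into line with it. The change is a worthwhile, inexpensive safety improvement, and nothing here shows that participants are being left without care.

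**What to change.** In the Safety Protocol:

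1. Have a positive weekly answer automatically alert the existing team psychologist, who then emails the participant at the registered address. Use the same rule in both arms, and do not show the arm in the alert, so that the blinding of trial researchers described under Randomization is kept.
2. Keep the weekly prompt, the clinician address given at entry and the referral information at assessments.
3. Repeat Study Setting's exception in the email-only sentence.
4. Because Results says that recruitment is underway, apply the change to all current and new participants from the date the ethics committee accepts it, and record that date.

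**Cost.** A small website change in mid-trial, wording changes in one section, a submission to the ethics committee, and psychologist time for each positive answer. The total time cannot be estimated from the document. No new data are collected and no extra staff role is needed.

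**Downsides.** Delivery becomes slightly less unguided than Strengths and Limitations describes. Some alerts will concern thoughts milder than the distress named in Study Setting. Participants handled before and after the change will have had different safety responses. Emails may go unread, particularly as Interventions allows pseudonymous addresses. The change adds a step started by the team; it does not guarantee contact.

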### Interventions

Access to the treatment website for each of the following conditions will be for a period of 10 weeks from the point of randomization.

The DEAL Project program is a 4-week psychological treatment delivered entirely via the Internet. Participants access the Internet-based sessions from their home computer (or other preferred port for Internet access). Participant-selected pseudonym usernames/emails serve as their login code for the website. Content of the sessions is based on cognitive behavior therapy (CBT) and motivational enhancement theory and was developed from the SHADE resource [59]. Major modifications to the SHADE resource included length, language, reduction of text content, modified design and flow of program, and incorporation of youth vignettes. Participants are asked to complete each session of the DEAL Project intervention in sequence, a week apart, from the point of randomization. The website tracks participants’ progress through each weekly module, with automated email reminders sent to the participant’s nominated email address. However, participants are not “locked out” between sessions so they may complete at a faster rate.

There were 4 sessions of the HealthWatch program that were chosen for this study. This is an attention-control condition program first developed for the Australian National University WellBeing Study [66] in which participants read information about various health concerns and complete accompanying surveys. The purpose of this condition is to control for time spent interacting with an Internet-based program. The specific modules and surveys selected for the four weeks (from the complete 12-week set) were those deemed to be more relevant to younger people and include environmental health, physical and mental activity, nutrition, and relationships. These were redesigned to match the DEAL Project in appearance. Preliminary evidence from the WellBeing research trial suggests that the site is not associated with a reduction in depressive symptoms over time in adults.

### Assessment and Outcome Measures

All assessment tools are frequently used in mental health and alcohol research and in Internet-based (nonface-to-face) formats. Table 1 shows the schedule of assessments.

**Table 1 table1:** Intended assessments and administration frequency.

Assessment instruments		Baseline assessment	Endpoint self-assessment (5 wks post baseline)	Follow-up self-assessments (12, 24 wks post baseline)
Demographics		✓	-	-
Service utilization		✓	-	-
**Depression**				
	Patient Health Questionnaire (PHQ-9) [67]	✓	✓	✓
	DASS-21 [62]	✓	✓	✓
**Alcohol**				
	AUDIT [63]	✓	✓^a^	✓^a^
	TOT-AL [68]	✓	✓	✓
	World Health Organization (WHO) Composite International Diagnostic Interview (CIDI-Alcohol) [69]	✓	✓	✓
